**Fig. 1 Fig1:**
[figure not shown]
CONSORT flow chart

People who express an interest in the study, will be interviewed face-to-face by one of the researchers (AO, LJ). During this interview, they will receive additional information about the study. When individuals fulfil the inclusion criteria of the study and want to participate, written informed consent will be obtained. Subsequently, the baseline assessment will be completed and the intervention will be carried out in the intervention group. At 12 months after inclusion in the study, participants will be approached again by the researcher to complete a face-to face follow-up assessment. With written permission of the participants, data will be extracted from medical files with the use of a checklist, 12 months post-inclusion.

The independent Ethics committee of Rotterdam (Medisch Ethische Toetsingscommissie) has given approval for the study to be performed.

### Statistical analysis

Analyses will be performed following the intention-to-treat principle. Descriptive statistics will be used to summarize characteristics of the residents, the care homes and of people receiving home care. Characteristics of participating individuals (age, gender, socio-economic status, educational level) will be compared at baseline between the intervention and control (usual care) group using independent sample t tests and Chi^2^ tests.

Multivariate analysis will be used to compare differences between the intervention group and the control group at baseline and to compare differences in changes after 12 months following the inclusion. Patient characteristics, TFI score, MMSE score and place of residence will be used as covariables. All statistical tests will be considered significant if *p* < 0.05. Missing items will be imputed by the peoples’ own average score if they have completed at least 50 % of the items.

The cost-effectiveness of ACP will be assessed by calculating the incremental cost-effectiveness ratio (ICER), defined as the difference in costs of ACP compared to usual care, divided by the average change in effectiveness, with the patient activation as primary outcome measure [17]. We will perform a sensitivity analysis to assess the stability of the results to changes in costs and effectiveness parameters. Because of the short time horizon, costs and effects will not be discounted.

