### Sample size

We aim at an overall power of 0.8 (alpha 0.05) to detect a difference of at least 0,5 SD in the Patient Activation Measure. We consider 0,5 SD to be a clinical relevant difference based on the article of Norman et al. [25]. To be able to detect such a difference we need 63 individuals in each arm in a non-clustered study. We used a multiplication factor of (1 + (k-1)*ICC), with k indicating the average cluster size, which is 12, and ICC indicating the intraclass correlation, which is the fraction of total variation in the data that is accounted for by between-group variation. For an ICC of 0.05 this amounts to a multiplication factor of 1.55, and thus 98 (1.55*63) individuals in both the intervention and the control arm.

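### The arms are compared on 12-month changes and baseline PAM is not named among the covariables; naming it would gain precision on the primary outcome with no new data

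*Protocol article*

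**What the plan says.** Under Statistical analysis, the protocol article plans a multivariate analysis "to compare differences in changes after 12 months following the inclusion". The next sentence gives the adjustment set: "Patient characteristics, TFI score, MMSE score and place of residence will be used as covariables". Two baseline scores (TFI and MMSE) are named individually; baseline PAM is not. The only characteristics spelled out in that section are age, gender, education and socio-economic status, and they appear in the sentence on baseline comparisons, not in the covariable sentence.

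Under Assessment and data collection, PAM-13 is measured by interview at baseline and again at 12 months in participants who are still competent. So the baseline value will be in the data set.

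Under Sample size, the target is "to detect a difference of at least 0,5 SD in the Patient Activation Measure". That section gives neither an SD of the change in PAM nor a correlation between baseline and follow-up.

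**The concern.** A change score subtracts the whole baseline value, whatever the correlation between the two measurements. Regression on the baseline subtracts only the part that predicts the follow-up value. When the correlation is imperfect, the change score therefore carries extra noise into the treatment contrast. Baseline PAM is likely to be among the stronger predictors of 12-month PAM, and nothing further need be collected to use it.

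At stake is precision on the primary outcome. With 98 per arm and an average cluster size of 12 there are only about 98/12 = 8 clusters per arm, so chance differences in baseline PAM between arms can be noticeable. The pairing of neighbourhoods is on income and does not balance PAM directly.

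**Working it through.** **Inputs from the Sample size section.** "We aim at an overall power of 0.8 (alpha 0.05"; a difference of 0.5 SD of PAM; "we need 63 individuals in each arm in a non-clustered study"; "with k indicating the average cluster size, which is 12"; "For an ICC of 0.05 this amounts to a multiplication factor of 1.55"; "thus 98 (1.55*63) individuals in both the intervention and the control arm".

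**Assumed, not in the documents.** Baseline-to-follow-up correlation rho (shown over a range); equal SDs of PAM at both times, set to 1; the same ICC of 0.05 for each form of the outcome; no gain from the other covariables; no dropout.

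**Step 1: reproduce the plan.** Two-sided alpha 0.05 and power 0.80 give n = 2 × (1.96 + 0.84)² / 0.5² = 62.7, that is 63 per arm. (Sidedness is not stated; a one-sided test would give 50, so two-sided is what was used.) The design effect is 1 + (12 − 1) × 0.05 = 1.55, and 63 × 1.55 = 97.65, that is 98. The stated figures reproduce as a comparison of means with the SD of PAM itself. Power at 98 per arm on that basis is 0.803.

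**Step 2: variances.** Relative to the variance of PAM:

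- change score: 2(1 − rho)
- adjusted for baseline PAM: 1 − rho²
- ratio: 2(1 − rho) / [(1 − rho)(1 + rho)] = 2/(1 + rho), which exceeds 1 for every rho below 1.

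**Step 3: power at 98 per arm.** Power = Φ(0.5 / √(2 × v × 1.55 / 98) − 1.96), with v the relative variance. The last column is the n per arm needed for 80% power.

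| rho | v, change | v, adjusted | ratio | power, change | power, adjusted | n per arm, change / adjusted |
|---|---|---|---|---|---|---|
| 0.3 | 1.40 | 0.91 | 1.54 | 66% | 84% | 137 / 90 |
| 0.4 | 1.20 | 0.84 | 1.43 | 73% | 87% | 118 / 83 |
| 0.5 | 1.00 | 0.75 | 1.33 | 80% | 90% | 98 / 75 |
| 0.6 | 0.80 | 0.64 | 1.25 | 88% | 94% | 80 / 64 |
| 0.7 | 0.60 | 0.51 | 1.18 | 95% | 98% | 59 / 52 |

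The change score has the variance the plan assumed exactly at rho = 0.5, since 2(1 − 0.5) = 1. Below that it has more, above it less. The adjusted variance never exceeds 1, so for any rho of 0 or more 98 per arm keeps at least the planned power.

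**Step 4: what a chance baseline difference does.** The standard error of the baseline PAM difference is √(2 × 1.55 / 98) = 0.18 SD. Given a baseline difference d, the change contrast shifts by −(1 − rho)d. For d of one standard error this is 0.09 SD at rho 0.5 and 0.12 SD at rho 0.3, or 18% to 25% of the 0.5 SD target. This is the loss of Step 2 seen conditionally on d, not a second loss.

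**The case against.** **Baseline PAM is unnamed, not excluded.** The covariable sentence uses the open term for patient characteristics, and the article is a condensed account whose full protocol and SAP are not shown. A comparison of changes could also be carried out as a regression of change on baseline. This stands as a limit on the claim: a reader might infer that the plan rules out baseline adjustment, and the text does not say so. But it does fix a comparison of changes and an adjustment list, and that list names two other baseline scores.

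**The trial is not shown to be undersized.** Because the calculation uses the SD of PAM and the analysis uses changes, a reader might infer that 98 per arm is wrong or too few. The documents do not support that. They give no rho, and at rho of 0.5 or more the change analysis meets or exceeds 80%. The ICC of change may also be below 0.05, since stable neighbourhood differences cancel. At rho 0.4, an assumed ICC of 0.027 for change gives 63 × 1.2 × (1 + 11 × 0.027) = 98, which restores the planned power. The listed covariables may add precision too.

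**Chance imbalance does not bias the change score.** Over repeated randomisations it is unbiased, so the cost is precision and not validity. This stands.

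**A change score has a use here.** People in the intervention group are invited to an information meeting about the study and the intervention, which is described before the consent interview. The Limitations section concedes that selection bias cannot be ruled out. If the arms differed systematically and stably at baseline, a change score would remove that difference while baseline adjustment could leave some of it. That is a fair reason to keep the change analysis as a sensitivity analysis. It does not remove the gain from adjustment in the primary model.

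**Conclusion.** The point holds as one of precision. Read as written, the primary comparison gives up precision that an already collected variable would supply, at any rho below 1. The excess variance is 54% at rho 0.3, 33% at 0.5 and 18% at 0.7. Whether power falls below 80% is conditional: it does so only for rho under 0.5, and the 66% at rho 0.3 also needs the ICC of 0.05 to hold for changes. Adjustment for baseline PAM removes this dependence on an unstated rho.

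All power figures rest on the assumptions listed with the calculation. They are before dropout, and the article expects some dropout and does not ask PAM of participants who have died or lost competence by 12 months. The change is worth making before the analysis is fixed; the stated sample size needs no correction on this account.

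**What to change.** Add baseline PAM to the listed covariables in the primary model, which should account for the neighbourhood clusters. The outcome may be 12-month PAM or the change in PAM: once baseline PAM is a covariate, both give the same treatment estimate, because subtracting the baseline from the outcome only lowers its own coefficient by 1. Likewise adjust SF-12 and PSQ for their own baseline values.

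Changes from baseline may still be reported. Because the procedures imply that recruitment follows cluster randomisation, keep an unadjusted change analysis as a prespecified sensitivity analysis.

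The cost is one line of wording in the protocol or SAP. No new data, visits or participants are needed.

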Also, research on the costs of ACP is limited, although the cost-effectiveness of health care interventions at the end of life is an important issue due to the fact that end-of-life care is often expensive. While health care costs in an average life year have been found to amount to 1100 € per person, costs per last year of life were 13,5 times higher and approximated 14,900 € per person according to Polder et al. [9]. Molloy et al. assessed the costs of an ACP program in a randomized controlled trial in Ontario, Canada. Intervention nursing homes reported fewer hospitalizations per resident, a lower hospital length of stay ensuing reduced hospital care costs and lower total health care costs than control nursing homes [10]. We are not aware of any formal cost-effectiveness studies on ACP programs in care homes or nursing homes in Europe.

We will perform the first cluster randomized controlled trial on the effects of ACP in frail, older people in the Netherlands. The main objective of this project is to assess the effects, the costs and the cost-effectiveness of ACP. Participants in the intervention group will be offered the Respecting Choices program, one of the most promising ACP programs (see below for further information about the program) [6, 11]. We focus on older people living in care homes or living at home and receiving home care. We hypothesize that ACP will lead to better patient activation in medical decision making and quality of life in the intervention group compared to the control group, while reducing futile interventions and thus health care costs.

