### Assessment and data collection

At baseline, in personal structured interviews, patient activation will be measured (PAM-13) [17]. The PAM assesses patients’ knowledge, skill and confidence in self- management. Also, generic Health-Related Quality of Life as measured by the SF-12 [18] and satisfaction with health care as measured by the PSQ-18-SF6 [19] will be assessed.

At 12 month follow-up participants will be interviewed again and their competence will be assessed with an adapted version of the Mini-Cog [20]. If participants are competent, the questions of the SF-12 [18], PAM [17], and PSQ-18-SF6 [19] will be asked. We will also ask whether participants completed an advance directive and assigned a proxy decision-maker. In the intervention group, open (qualitative) questions will be asked about how the patient experienced the ACP program.

If the Mini-Cog indicates that participants are no longer competent, a proxy, assigned by the patient at the start of the study, will be approached for a telephone interview. This interview will include the PSQ-18-SF6 [19] and a caregiver activation measure (CAM) [21]. Completion of an advance directive and assignment of a proxy decision-maker by the participant will be assessed. In the intervention group, open (qualitative) questions will be asked about how the relative and the patient experienced the ACP program.

If people pass away during the 12 month follow-up, a proxy, assigned by the patient at the start of the study, will be approached for a telephone interview. This interview will address characteristics of the dying process, quality of dying [16], PSQ-18-SF6 [19], feelings of anxiety and depression of the relative as measured by the HADS [22]. In the intervention group, open (qualitative) questions will be asked about how the relative and the patient experienced the ACP program.

In a medical file study, we will investigate whether people have an advance directive in their medical file (and study its content). Moreover, we will study the medical care people receive during 12 months after inclusion, such as hospitalizations (number, length of stay), use of homecare, palliative care, diagnostic procedures and specific treatments (e.g. medication, mechanical ventilation, resuscitation, chemotherapy, artificial fluids or food, surgery or antibiotics).

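### The ICER pairs a cost difference measurable in all participants with a PAM change that exists only for competent survivors

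*Protocol article*

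**What the plan says.** In the protocol article, Statistical analysis defines the ICER as the cost difference between ACP and usual care "divided by the average change in effectiveness, with the patient activation as primary outcome measure". The same section commits to intention-to-treat, imputes missing items only for people who completed at least half of a scale, and plans a sensitivity analysis on cost and effectiveness parameters.

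Assessment and data collection fixes who has which data at 12 months:

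- Competent survivors: "If participants are competent, the questions of the SF-12 [18], PAM [17], and PSQ-18-SF6 [19] will be asked".
- Survivors no longer competent: a proxy answers the satisfaction scale and a caregiver activation measure (CAM). There is no PAM and no SF-12.
- Decedents: a proxy is interviewed. "This interview will address characteristics of the dying process, quality of dying [16], PSQ-18-SF6 [19], feelings of anxiety and depression of the relative". There is no activation measure.
- Resource use, from medical files: "we will study the medical care people receive during 12 months after inclusion, such as hospitalizations". This is not limited to competent survivors.

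The Background makes cost-effectiveness part of the main objective. It motivates the question by the expense of the last year of life: "While health care costs in an average life year have been found to amount to 1100 € per person", whereas "costs per last year of life were 13,5 times higher and approximated 14,900 € per person".

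**The concern.** An incremental ratio is interpretable when cost and effect are averaged over the same people. Here the effect has no value for anyone who dies or loses competence, while the cost does. For people who die, PAM is undefined rather than missing, so imputation could not properly supply it.

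Two readings of the plan remain. If costs cover everyone, the ratio mixes two populations. If costs are limited to PAM completers, the groups compared are selected on survival and competence after randomisation, and the end-of-life care that motivates the economic question drops out. Someone following the plan could do either and report a different result.

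**Working it through.** **Plan's own figure.** 14,900 / 1,100 = 13.5, which agrees with the ratio in the Background.

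**Inputs.**
- Cost in an average life year, 1,100 euro, and in the last year of life, 14,900 euro (Background).
- Life expectancy 3.7 years (Study population, for care-home residents; Limitations, for the study group).
- Follow-up 12 months (Limitations).
- Assumed: constant hazard, because no death rate is given. 12-month mortality d = 1 − exp(−1/3.7) = 23.7%.
- Assumed: survivors' annual cost S = 1,100, 5,000 or 10,000 euro. The article gives no cost for frail surviving care users.
- Assumed: decedents' cost within follow-up D = 14,900 euro. The low case is 7,450 euro (14,900 / 2), as if deaths and last-year spending were spread evenly, since costs are counted only from inclusion.

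**Decedents' share of total cost** = d × D / (d × D + (1 − d) × S).

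Per participant, d × D is 0.237 × 14,900 = 3,529 euro, or 1,764 euro in the low case. (1 − d) × S is 839, 3,816 or 7,632 euro (d unrounded throughout).

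| S (euro) | D = 14,900 | D = 7,450 |
|---|---|---|
| 1,100 | 3,529 / 4,368 = 81% | 1,764 / 2,604 = 68% |
| 5,000 | 3,529 / 7,345 = 48% | 1,764 / 5,580 = 32% |
| 10,000 | 3,529 / 11,160 = 32% | 1,764 / 9,396 = 19% |

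With D = 14,900 and S = 1,100, the share is 60% at 10% mortality and 71% at 15%. It passes one half at 1,100 / (1,100 + 14,900) = 6.9%.

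Decedents are 23.7% of participants. Their share exceeds that whenever a decedent costs more within follow-up than a survivor, which holds in every cell except the last (19%).

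**Effect on the numerator.** Suppose, as illustration only, that ACP lowers decedents' costs by 20% and leaves survivors' costs unchanged:
- All randomised: −0.20 × 14,900 × 0.237 = −706 euro per person.
- PAM completers only: 0 euro.

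The same data then give a saving or none, depending on whose costs enter the ratio.

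**Do other provisions settle it?** The item rule needs half a scale completed, so it cannot supply a wholly absent PAM. The sensitivity analysis, as described, varies parameters and not the population. The CAM is a different instrument answered by another person, and it is not used after death.

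**The case against.** A reader might infer that people who die or lose competence carry most of the costs and that the ICER therefore cannot answer the cost-effectiveness question. The documents do not support that. The 1,100 euro describes an average life year, whereas surviving participants are frail, aged 75 or over and receiving care, and care-home days are themselves costed. The 14,900 euro covers a full last year, of which only part may fall after inclusion. The 3.7 years is given in Study population for care-home residents, while home-care clients are also enrolled. Nothing is said about the number or cost of people who lose competence. These objections stand, and they rule out a majority share as a finding. It is also too absolute to say that the question cannot be answered: the cost difference can be estimated in everyone whose file is extracted, and a rule for deaths would make the ratio interpretable.

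Two further complaints fail. The denominator might look like a change within one arm, but the ratio is called incremental, and the preceding paragraph compares changes between groups, so the between-arm reading is the natural one. Nor do the documents support faulting cost per PAM point for lack of a decision threshold; using the declared primary outcome as the effect unit is a coherent choice.

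Finally, handling of missing data may sit in a fuller plan. That is fair for imputation details. It does not remove the mismatch, which follows from choices this article fixes: the effect measure, who is asked it, whose costs are collected, and intention-to-treat.

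**Conclusion.** The point holds in limited form. As defined, the ICER has no effect value for participants who die or lose competence, and nothing in the article says how they enter it. It therefore either combines two populations or omits end-of-life costs and departs from intention-to-treat.

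Decedents probably carry a disproportionate share of cost: 32% to 81% for survivor costs of 10,000 down to 1,100 euro, with 23.7% mortality and the full last-year cost. The share is lower if only part of that cost falls within follow-up. The range rests on an assumed constant hazard and assumed survivor costs, so it shows that the choice of population can matter and does not predict the trial's result. The change should be made because cost-effectiveness is part of the main objective; the primary PAM comparison does not depend on it.

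**What to change.** 1. Report the between-arm difference in mean cost in all randomised participants as a result in its own right.
2. Compute cost per PAM point with the same participants in numerator and denominator, and label it as applying to competent survivors only. State that the denominator is the between-arm difference in change.
3. Add a cost-utility analysis in all randomised participants: utilities derived from the SF-12, 0 from the date of death, imputation for survivors without a follow-up SF-12, and clustering respected. Unlike PAM, a QALY is defined after death, so decedents can enter both parts of the ratio.

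The cost is extra analysis of data already planned, provided the date of death is recorded. The SF-12 ("generic Health-Related Quality of Life as measured by the SF-12") is planned at baseline and 12 months. Three downsides should be stated. Two time points give coarse QALYs. Utilities of survivors who lose competence rest on imputation, because the follow-up SF-12 is also limited to competent participants. The QALY result depends partly on survival, which is not a listed outcome. For these reasons the cost-utility analysis is proposed alongside the PAM ratio and not as its replacement.

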## Discussion

The presented study measures the costs and effects of ACP in elderly care. Until now, the costs and effects of ACP in Dutch care homes have not been studied in a randomized controlled trial. Currently, ACP is encouraged and several studies showed that ACP is associated with beneficial effects on patient outcomes [6, 7]. However, we do not know whether these beneficial effects apply to frail, older people residing in Dutch nursing homes or living at home and receiving home care. The presented study aims at studying whether offering ACP to older people will improve patient activation, quality of life and satisfaction with care, while reducing futile medical interventions. Trained facilitators will talk with frail, older people about their wishes and preferences concerning medical treatment and care, facilitate timely conversations between participants and their appointed proxy decision-maker and support them in establishing an advance directive. This study will contribute to the implementation of an evidence-based ACP program for older people in The Netherlands. Below, some strengths and limitations of the study will be discussed.

